### 2.5. Intervention Procedures

The cognitive rehabilitation protocol (5 weeks, 3 sessions/week, 45 min/session) will be delivered to all participants according to the corresponding experimental group:-30 CNDs patients will receive home-based cognitive rehabilitation activities with an innovative digital solution for remote rehabilitation of cognitive difficulties (tele@cognitive group);-30 CNDs patients will receive home-based unstructured cognitive rehabilitation treatment (Active Control Group—ACG).

The technological solution that will be applied in the tele@cognitive group consists of: (a) a telemedicine platform (RICORDO platform), which allows prescription and planning of digital content for cognitive rehabilitation and monitoring of the rehabilitation cycle and (b) RICORDO application [http://www.ricordo-dtx.com/ (accessed on 10 January 2025)] that will be downloaded on tablets provided to patients by the recruiting units, which will allow the patient to benefit from personalized rehabilitation treatment remotely and in asynchronous mode. In detail, through RICORDO platform, the clinician will have the possibility of prescribing, within the patient’s Individual Rehabilitation Plan (PRI), a personalized intervention that will involve the use of libraries of digital rehabilitation content that maps all the neurocognitive domains provided for in the most recent version of the Diagnostic and Statistical Manual of Mental Disorders (DSM-5) [102]. In particular, the rehabilitation program will include cognitive activities focused on cognitive domains, such as executive functions, memory (long-term memory of both verbal and visuospatial type, autobiographical memory, and semantic memory), attention (selective attention and divided attention), and spatial–temporal orientation and language. Each cognitive exercise will be structured into five levels of difficulty that adaptively increase (algorithms on both subject’s performance and perceived difficulty). All data on patient progress and adherence will be collected and will be available to evaluate and monitor the results of rehabilitation.

The unstructured cognitive rehabilitation treatment applied in the ACG will offer paper–pencil cognitive activities that will stimulate the same cognitive abilities indicated in the innovative digital solution. Subjects assigned to ACG will be requested to work for the same duration and frequency as the tele@cognitive group; they will receive from the therapist an instructions booklet and a participant diary.

### 2.6. Outcome Measures

#### 2.6.1. Primary Outcome Measures

The primary outcome measures for this study will be the change from the baseline (T0) to post-treatment (T1) and 3-month follow-up visit (T2) in:Montreal Cognitive Assessment (MoCA). MoCA [96] is a screening test for global cognitive functioning. It includes tasks involving several cognitive domains: visuospatial, executive function, naming, selective and sustained attention, language, abstraction, memory, and orientation (score range min = 0, max = 30, higher score = better outcome).Long-term episodic verbal memory as assessed by Free and Cued Selective Reminding Test (FCSRT). FCSRT [103] is a measure of long-term episodic verbal memory. It provides five scores: Immediate Free Recall (IFR, spontaneous recall across three trials; score range min = 0, max = 36), Immediate Total Recall (ITR, total recall across three trials; score range min = 0, max = 36), Delayed Free Recall (DFR, score range min = 0, max = 12), Delayed Total Recall (DTR, score range min = 0, max = 12). Higher scores indicate better performance. Finally, the Index of Sensitivity to Cueing (ISC, score range min = 0, max = 1) reflects the difference between the number of items recalled spontaneously and the number of items recalled with the help of cues. A higher ISC indicates a greater sensitivity to cues.

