### 2.2. Randomization and Blinding

The assigned group will be obtained by stratified randomization (1:1 ratio), according to clinical condition, age, and his/her performance in the Montreal Cognitive Assessment (MoCA) test [94,95,96]. Stratified randomization will be achieved by generating a separate block for each combination of covariates, and participants will be assigned to the appropriate block of covariates by a researcher blinded to the study’s aims. Details of the allocated group will be given on cards contained in sequentially numbered, opaque, and sealed envelopes. A blinded researcher will conduct the evaluations.

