### 2.3. Sample Size

In the RCT, patients will be assigned to either receive tele@cognitive protocol or a home-based unstructured cognitive stimulation (ACG). The sample size of the present study was estimated on the basis of a previous work on people within the Alzheimer’s Disease continuum [3] and it was computed on a primary outcome variable (an increase in MoCA score). Applying a two-tailed independent samples *t*-test (alpha = 0.05, beta = 0.80) and considering the effect size (d = 0.784) between two types of intervention (tele@cognitive vs. ACG), we obtained a minimum sample size of 60 subjects (30 per group), taking into account the drop-out rate.

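### Several unranked primary outcomes at two visits, while the sample size covers one MoCA test with no visit named

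*Protocol article*

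**What the plan says.** Section 2.6.1 opens with "The primary outcome measures for this study will be the change from the baseline (T0) to post-treatment (T1) and 3-month follow-up visit (T2"), followed by two items of equal standing: MoCA, and long-term verbal memory measured by FCSRT. Of FCSRT it says "It provides five scores" (IFR, ITR, DFR, DTR and ISC). It does not say which score, which instrument or which visit leads.

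Section 2.3 rests on one outcome: "it was computed on a primary outcome variable (an increase in MoCA score"). The test is set out as "Applying a two-tailed independent samples" t-test, with "alpha = 0.05, beta = 0.80) and considering the effect size (d = 0.784) between two types of intervention". The result is 60 participants, 30 per group, with an allowance for drop-out whose rate is not given. The section does not say whether the MoCA increase is measured at T1 or T2.

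Section 2.8 plans a repeated-measures analysis over T0, T1 and T2 for the two groups, within-group paired tests, and a further between-group comparison by t-test, ANCOVA or a non-parametric test. It ranks none of these and does not say which one decides the primary question.

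**The concern.** The sizing describes a trial with one deciding test. The outcome section describes a trial with several. Both statements stand in the same article and they do not match.

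Two things are at stake. First, a favourable result on one FCSRT score at one visit could be reported as a positive primary outcome even if MoCA, the only outcome the trial was sized for, shows nothing. The 5% in section 2.3 does not describe the error rate of such a claim. Second, if the error rate were later protected by splitting alpha over the listed outcomes, the power intended in section 2.3 would no longer apply.

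**Working it through.** **Inputs.** From section 2.3: two-sided alpha 0.05, d = 0.784, 30 per group. The article prints "alpha = 0.05, beta = 0.80"; only reading 0.80 as power reproduces the sample size, so I treat it as a labelling slip. From section 2.2: "stratified randomization (1:1 ratio"). From section 2.6.1: MoCA, five FCSRT scores, two visits. Assumed, because the article gives no figure: 10% drop-out, and all correlations between scores and between visits.

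**Step 1: the plan's own figure.** A two-sided independent t-test with d = 0.784, alpha 0.05 and power 0.80 needs 26.5, so 27 per arm, or 54 in total. With 10% drop-out, 54 / 0.90 = 60. The stated size reproduces for one test. (Drop-out of 5% gives 57 and 15% gives 64.)

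**Step 2: how many primary tests there are.** The text allows at least four readings:
- 2 tests: MoCA and one FCSRT score, one omnibus repeated-measures test each.
- 4 tests: the same two scores, each at T1 and T2.
- 6 tests: MoCA and five FCSRT scores, one omnibus test each.
- 12 tests: (1 + 5) scores × 2 visits.

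**Step 3: chance of at least one false positive when each test is at 0.05.** For k independent tests this is 1 − 0.95^k. For correlated tests I used simulation of two-sided normal tests with no true effect (400,000 draws), treating each omnibus test as a single such test. The first column gives the assumed correlations in the order MoCA with FCSRT / among FCSRT scores / T1 with T2.

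| Correlations | 2 tests | 4 tests | 6 tests | 12 tests |
|---|---|---|---|---|
| Independent | 9.8% | 18.5% | 26.5% | 46.0% |
| 0.1 / 0.3 / 0.5 | 9.7% | 17.3% | 24.9% | 40.9% |
| 0.3 / 0.5 / 0.5 | 9.5% | 16.9% | 21.8% | 36.4% |
| 0.4 / 0.7 / 0.7 | 9.3% | 15.3% | 18.2% | 28.6% |
| 0.5 / 0.8 / 0.7 | 9.0% | 14.9% | 16.0% | 25.1% |

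The lower ends move by a point or so with the correlations chosen. Raising the T1–T2 value in the last row to 0.8 gives 14.0% for four tests and 23.8% for twelve. A common correlation of 0.8 among all twelve gives about 19%.

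**Step 4: power if alpha is split equally (0.05/k), d = 0.784.** The 27 completers per arm are 30 less the assumed 10%.

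| Tests | Alpha each | Power, 30 per arm | Power, 27 per arm | Per arm for 80% (total with 10% drop-out) |
|---|---|---|---|---|
| 1 | 0.05 | 84.8% | 80.7% | 27 (60) |
| 2 | 0.025 | 76.7% | 71.5% | 33 (74) |
| 4 | 0.0125 | 67.6% | 61.7% | 38 (85) |
| 6 | 0.0083 | 62.1% | 55.8% | 42 (94) |
| 12 | 0.0042 | 52.5% | 46.1% | 47 (105) |

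Equal splitting is the simplest case. The article does not plan it; the table shows only what such a split would cost.

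**The case against.** Five objections deserve an answer.

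- **Twelve primary tests.** A reader might infer twelve, with a false-positive risk of 25–45%. The article does not establish that. The five scores appear in the description of the instrument, and the repeated-measures analysis in section 2.8 could give one test per score across visits. Twelve is one possible reading. Section 2.8 also adds separate between-group tests without fixing their number, so none of the four readings can be excluded.
- **The success rule.** The article does not say that one success is enough. If every primary outcome had to succeed, there would be no inflation, and the cost would fall on power. The percentages in step 3 therefore apply only under an at-least-one rule.
- **Multiplicity belongs in the SAP.** This is a journal article, and the SAP and full protocol are not shown. A reader might conclude that the trial has no alpha control; that cannot be said from this text. But the list of primary outcomes and the outcome used for sizing are both fixed here, and they disagree. An SAP that split alpha would undo the power in section 2.3. One that chose a single endpoint would contradict section 2.6.1.
- **It is a pilot.** Section 2.1 calls it one. Yet section 1 sets out to test short- and long-term efficacy against the active control, and section 2.3 is a formal power calculation for that comparison.
- **MoCA is the natural lead.** It is the only outcome singled out anywhere, which supports the fix below. Section 2.6.1 still gives FCSRT the same status.

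**Conclusion.** The point holds as a mismatch between sections 2.6.1 and 2.3. Under an at-least-one-success rule the error rate exceeds the stated 5% on every reading: about 9–10% (two tests), 15–19% (four), 16–26% (six) or 25–46% (twelve). These ranges rest on assumed correlations, and very high correlation throughout would bring the twelve-test figure to about 19%. If alpha is split equally, power per test with 30 per arm drops below 80% for any split into two or more. The article does not support a single headline error rate, and the sample size is not wrong: 60 is adequate for one MoCA test with about 10% drop-out.

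**What to change.** In section 2.6.1, name one primary endpoint that matches the sizing: the between-group difference in MoCA change from T0 to one stated visit, for example T1. Name the same visit in section 2.3. Make MoCA at the other visit and one pre-named FCSRT score key secondary outcomes, tested in fixed order or by Holm's method. List the remaining FCSRT scores as secondary or descriptive. The choice of visit and of FCSRT score is the sponsor's, and it should be made before anyone sees unblinded data, because a choice made afterwards gives no protection.

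The cost is a change of wording in two sections, and in the SAP and registry entry if they carry the same list. No extra data or participants are needed and 60 stays valid. The downside is that FCSRT loses equal primary status. Keeping MoCA and one FCSRT score as two primaries with alpha split equally would instead need about 74 participants at the same effect size and the assumed 10% drop-out.

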#### 2.6.2. Secondary Outcome Measures

The secondary outcome measures for this study will be the change from the baseline (T0) to post-treatment (T1) and 3-month follow-up visit (T2) in:Quality of life as assessed by EQ-5D-3L. EQ-5D-3L [104] is a measure of health status consisting of five dimensions (mobility, self-care, usual activities, pain/discomfort, and anxiety/depression). Each dimension has three response levels (no problems, some problems, unable to/extreme problems). In addition, the questionnaire includes a visual analog scale that records the patient’s perception of his or her overall health (score range min = 0, max = 100, higher score = better outcome).Non-motor experiences of daily living as assessed by MDS-UPDRS scale, part I. MDS-UPDRS scale [105], part I (only for the PD group) is a measure of non-motor experiences of daily living consisting of a total of 13 questions (score range min = 0, max = 52, higher score = worse outcome).Motor abilities as assessed by MDS-UPDRS scale, part III. MDS-UPDRS scale [105], part III (only for the PD group) is a measure of motor abilities consisting of a total of 18 questions with 33 individual items. Each item has a 0–4 rating, where 0 = normal, 1 = slight, 2 = mild, 3 = moderate, and 4 = severe (score range min = 0, max = 132, higher score = worse outcome).Depressive symptoms as assessed by Hamilton Depression Rating Scale (HDRS). HDRS [106] is a measure of severity of the depressive symptoms consisting of a total of 21 items (score range min = 0, max = 64, higher score = worse outcome).Anxiety symptoms as assessed by State-Trait Anxiety Inventory (STAI-Y). The STAI-Y [107] consists of two 20-item scales providing separate measures of state and trait anxiety (S-Anxiety and T-Anxiety). Each scale has a score range from a minimum of 20 to a maximum of 80, with a higher score on the scale indicating a worse outcome.Behavior and personality as assessed by Neuropsychiatric Inventory (NPI). NPI [108] is used for assessing various neuropsychiatric symptoms. The inventory consists of 12 core domains, each reflecting specific neuropsychiatric symptoms. Each symptom is rated for both frequency and severity (score range min = 0, max = 144, higher score = worse outcome).Memory complaints as assessed by Everyday Memory Questionnaire (EMQ). EMQ [109] is a 20-item questionnaire that evaluate the frequency and impact of memory problems in daily life (score range min = 20, max = 180, higher score = worse outcome).Non-verbal abstract reasoning as assessed by Raven’s Colored Progressive Matrices (CPM). CPM [110] is a measure of non-verbal abstract reasoning (score range min = 0, max = 36, higher score = better outcome).Attentional abilities as assessed by Trial Making Test (TMT). TMT (Part-A and Part-B) [111] is a measure of attentional abilities, visuo-conceptual and visual–motor tracking. TMT-Part A involves visual scanning, number recognition, number sequencing, and motor speed. TMT-Part B assesses mental flexibility in managing more than one stimulus at a time and in shifting the course of an ongoing activity. High execution times indicate poor performance (score range min = n/a, max = no limits).Executive abilities as assessed by Stroop Test. Stroop Test [112] is a measure of executive abilities, including visual attention, selective attention, cognitive flexibility, and inhibitory control of behavior. Two scores are calculated with consideration of the number of errors and the time taken to complete all parts. High execution times and high numbers of errors indicate poor performance.Constructional praxia as assessed by Rey–Osterrieth Complex Figure-Copy (ROCF). ROCF [113] is a measure of constructional praxia (score range min = 0, max = 36, higher score = better outcome).Fluency abilities as assessed by Verbal Fluency (semantic and phonemic). Verbal Fluency (semantic and phonemic) [114] is a measure of verbal and semantic fluency abilities, executive functions abilities, lexical store size, lexicon access, and lexical organization (score range min = 0, max = no limits, higher score = better outcome).Nonverbal long-term memory as assessed by ROCF-Recall. ROCF-Recall [113] is a measure of nonverbal long-term memory (score range min = 0, max = 36, higher score = better outcome).

#### 2.6.3. Surrogate Outcome Measures

The surrogate outcome measures will be the change from the baseline (T0) to post-treatment (T1) in:Neurofilament light chain (NF-L) and Tau levels.Aß1-40, Aß1-42, p-tau-181, p-tau-231, and alpha-synuclein levels.Glial Fibrillary Acidic Protein (GFAP), chemokines, and sTREM2 levels.Neurogranin and Brain-Derived Neurotrophic Factor (BDNF) levels.Concentration and size of plasma Extracellular Vescicles (EVs).Resting Motor Threshold (rMT). rMT reflects membrane excitability of corticospinal neurons. Lower values indicate increased excitability.Motor Evoked Potentials (MEPs). MEPs are muscle twitches resulting from complex descending corticospinal volleys occurring after TMS pulses. MEP amplitude and latency reflect the integrity of the corticospinal tract and corticospinal excitability.Short-interval intracortical inhibition (SICI). TMS-SICI reflects inhibitory interneuronal circuits acting via GABA A receptors [115].Short-latency afferent inhibition (SAI). TMS-SAI reflects cholinergic transmission [116].

### 2.7. Data Collection

Demographic characteristics and cognitive reserve, evaluated with the Cognitive Reserve Index—questionnaire (CRI-q [116]), will be collected at the baseline evaluation (T0). The same trained neuropsychologist (blinded to patient treatment allocations) will assess primary and secondary outcome measures for a single patient in all visits (T0, T1, and T2). Neurophysiological and biomolecular data will be collected only at the baseline (T0) and at post-treatment (at 5 weeks, T1). A subjective assessment of the digital system’s usability will be performed at T1 using the System Usability Scale (SUS) [117], a 10-item attitude Likert scale. Best practices and standards will be adopted for the collection, storage, and treatment of the data. Clinical, functional, neurocognitive, and quality of life assessment data will be collected by clinicians and stored in a specific dataset. Data will be pseudo-anonymized so that they will not be linkable to the identities of the subjects. Neurophysiological data will be organized according to Brain Imaging Data Structure (BIDS) for non-invasive brain stimulation studies and safely stored in a dataset. Biological samples collected at T0 and T1 will be stored at −80 °C until the analyses. Biomolecular data will be safely stored in a dataset. Informed consent will be obtained from patients for the storage of all data. In more detail, the data collection in terms of data collected and tools will include:

[AIM1] Clinical, functional, neurocognitive, and quality of life data recorded at T0 (baseline), T1 (post-treatment, at 5 weeks), and T2 (3-month follow-up visit).

[AIM2] Neurophysiological data and blood samples will be collected at T0 and T1. Specifically:-Aß1-40, Aß1-42, p-tau-181, p-tau-231, NF-L, tau, GFAP, BDNF, Eotaxin-1, Eotaxin-3, alpha-synuclein, neurogranin, and sTREM2 will be measured in plasma or serum by commercially available kits. Coefficients of Variation (CVs) within-run will be accepted when in agreement with information from kit vendors. The concentration and size distribution of EVs will be assessed in light scattering mode with NanoSight NS300 instrument (Malvern, Worcestershire, United Kingdom). Samples will be diluted to obtain an optimal range of 20–150 particles/frame. For each sample, 5 videos of 60″ will be recorded and data will be processed using NanoSight NTA 3.2 software. Optimized post-acquisition settings will be kept constant during the analysis of all samples. Data obtained will be analyzed by comparing concentration (particles/mL), size distribution (nm), and their ratio (conc./size).-In each TMS recording session, i.e., at T0 and at T1, CNDs participants will be comfortably seated in a dimly lit room and neurophysiological measures will be collected while they are at rest: (a) the resting motor threshold (rMT), defined as the lowest transcranial stimulus intensity at which TMS of motor cortex produces an EMG response in half of the trials, will be estimated with a probability density function; (b) motor-evoked potentials (MEPs) will be collected at stimulation intensity equal to 120% of the resting motor threshold; (c) SICI will be obtained by delivering a TMS pulse at 70% of rMT at 1, 2, 3, 5 ms before the test stimulus; (d) SAI will be measured as change in MEPs when TMS is delivered after the electrical stimulation of the median nerve at different intervals (−28, −24, −20, −16 ms). These measures will be collected by targeting the cortical motor hotspot of the first dorsal interosseous muscle (FDI) on the left hemisphere while measuring responses from muscles of the hand. The position of the coil will be monitored throughout the duration of the experiment, thanks to a neuronavigation system that allows the coil to remain in correspondence with the target area.

[AIM3] By employing a diverse range of data collection instruments and analysis techniques, we aimed to gain a comprehensive understanding of treatment effects on cognitive function. In particular, this multifaceted approach involves capturing and analyzing various aspects related to cognitive performance: clinical, functional, neurocognitive, and quality of life measures, biochemical data derived from blood samples, different parameters derived from TMS experiments, and the data gathered during the rehabilitation program.

### 2.8. Statistical Analysis

A repeated-measures analysis will be used to compare pre-treatment (T0) versus post-treatment (T1) and follow-up (T2) clinical, functional, neurocognitive, and quality of life variables for the two groups. Neurophysiological and biochemical data will be analyzed using repeated-measures ANOVAs by comparing the data recorded at T0 and T1. Statistical tests suitable for the data type will be employed to assess the differences between the groups. For continuous variables, independent *t*-tests will be utilized, while chi-square tests will be applied for categorical variables [117,118]. This analysis will verify the effectiveness of the randomization procedure, ensuring that any subsequent comparisons or evaluations between the groups are reliable and valid.

Within-group analyses will be conducted for the tele@cognitive and ACG groups to examine changes from T0 to T1 and T2. Paired *t*-tests or Wilcoxon signed-rank tests, depending on data distribution, will be employed to assess the effectiveness of the intervention over time by analyzing the variations in the collected multimodal parameters [118,119]. Furthermore, a between-group analysis will be conducted to quantitatively compare the outcomes of the two groups. Statistical tests such as independent *t*-tests, analysis of covariance (ANCOVA), or non-parametric tests will be employed, depending on the distributional assumptions and nature of the outcome variables [118,120].

In addition to these statistical analysis, predictive modeling will be implemented to identify key factors associated with treatment outcomes by integrating multimodal data from cognitive assessment, neurophysiological evaluations, biomolecular patterns, and user interaction data within a sophisticated AI framework. Given the heterogeneous nature of the data collected from multiple sources, feature selection is essential to identify the most informative features and reduce dimensionality. This step is critical to eliminate redundant or irrelevant variables and improve model performance [121]. Statistical methods such as chi-square tests and mutual information will be employed to identify significant predictors associated with positive treatment outcomes [122]. Specifically, the dataset will include baseline clinical, functional, neurocognitive, and quality of life measures, biomolecular markers, and neurophysiological parameters.

Data will be preprocessed to clean and normalize them appropriately. These will include handling missing values (e.g., using imputation for continuous variables and mode replacement for categorical variables), standardizing features to a common scale, and encoding categorical variables as needed. Machine learning algorithms, such as random forests, support vector machines, naive bayes classifiers, and ensemble techniques, will be applied to develop predictive models for treatment outcomes using the collected information [123]. Model performance will be assessed using cross-validation techniques like leave-one-out or Kfold, and parameters will be fine-tuned using grid search techniques to optimize model performance [124]. To ensure generalizability, performance will also be evaluated using metrics such as accuracy, precision, recall, and area under the ROC curve (AUC-ROC), depending on the nature of the prediction task.

For tasks involving high-dimensional or complex data, such as neurophysiological signals or time-series patterns, deep learning architectures (e.g., convolutional neural networks for spatial data, recurrent neural networks for temporal data) will be employed. These models will be customized and optimized using grid search to ensure they are well-suited to the specific characteristics of the data.

After model training, explainable AI (XAI) techniques, such as SHAP (Shapley Additive exPlanations) values will be employed to interpret the model’s predictions and quantify the contribution of each feature to the outcome [125]. SHAP values provide a unified measure of feature importance by assessing the impact of individual features on the model’s output, not only enhancing the clinical interpretability and transparency of the predictive models but also providing insights into which factors are most influential in driving treatment outcomes.

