In particular, the first aim will be to assess the short-term and long-term efficacy of tele@cognitive protocol as compared to an unstructured cognitive at-home rehabilitation in the treatment of a cohort of patients with CNDs, monitoring intervention effectiveness by a clinical, functional, neurocognitive, and quality of life assessment applied before treatment (T0), after treatment (5 weeks, T1), and at a 3-month follow up visit (T2). We hypothesize that this digital health at-home intervention would ameliorate cognitive abilities more than unstructured at-home rehabilitation in subjects with SCCs, MCI, and PD. We will also evaluate adherence to the rehabilitation program delivered at-home in the absence of therapist supervision. It is hypothesized that, at an early stage of the disease, cognitive telerehabilitation treatment with innovative digital solutions can bring about positive effects on treatment adherence and difficulties specific to each clinical condition.

The second aim will be to investigate the effects of a cognitive rehabilitative protocol based on a digital health at-home intervention (tele@cognitive) on biomolecular and neurophysiological markers, hypothesizing that people with CNDs enrolled in the tele@cognitive protocol will develop changes in circulating biomarkers and patterns of connectivity. Specifically, at T0 and T1, we will study the effect of tele@cognitive treatment on: i) blood biomarkers reflecting neurodegeneration, amyloid-β, tau and alpha-synuclein pathologies, neuroinflammation, synaptic function, and neuronal communication; ii) neurophysiological responses to TMS over the motor cortex. This approach will give a broad overview of the circuits modulated through telerehabilitation (tele@cognitive treatment), possibly highlighting differential effects between the groups.

Finally, the third aim will be to investigate potential cognitive, neurobiological, and neurophysiological predictors of treatment outcomes in people with CNDs who received innovative technology-enhanced telerehabilitation intervention (tele@cognitive group).

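### Drop-out is expected, but the tests named for MoCA and FCSRT use only participants with the visit tested, so the T2 comparison can be biased if loss after T1 depends on response and differs by arm

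*Protocol article*

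**What the plan says.** Section 2.6.1 makes MoCA and FCSRT the primary outcomes, each as change from T0 to T1 (5 weeks) and to T2 (3-month follow-up).

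Section 2.8 describes the longitudinal analysis of the clinical and cognitive variables in general terms: "A repeated-measures analysis will be used to compare pre-treatment (T0) versus post-treatment (T1) and follow-up (T2". The type of model is not given. The next sentence does name one, but for other data: "Neurophysiological and biochemical data will be analyzed using repeated-measures ANOVAs by comparing the data recorded at T0 and T1". The section then lists paired t-tests or Wilcoxon tests within each arm, and independent t-tests, ANCOVA or non-parametric tests between arms.

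Drop-out is foreseen. Section 2.3 states: "we obtained a minimum sample size of 60 subjects (30 per group), taking into account the drop-out rate". No rate is given. The Introduction, under the first aim, says that the trial will evaluate "adherence to the rehabilitation program delivered at-home in the absence of therapist supervision".

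The one rule for missing values, imputation or replacement by the mode, comes later in section 2.8, as data preparation for the machine-learning models.

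**The concern.** The drop-out allowance in the sample size protects power. It does not protect against selective loss. An independent t-test, ANCOVA or rank test at T2 needs a T2 value, and a paired T0-T2 test needs both visits. Someone seen at T1 but not at T2 leaves the T2 comparison, and the T1 value, which says something about how that person was doing, is not used.

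The arms differ in what participants do at home: an adaptive tablet application in one, a paper booklet with a diary in the other. The reasons for not returning could therefore differ by arm. If those who gained least by T1 are less likely to return in one arm, that arm's T2 mean is calculated on a favourable selection. The T2 contrast is the trial's evidence for a long-term effect.

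**Working it through.** **1. The plan's own figure.** Section 2.3 gives an independent-samples t-test, two-sided alpha 0.05, d = 0.784, and 0.80 (printed as beta, read here as power). The noncentral t gives 26.53, so 27 per arm, or 54 in total. The stated figure is 30 per arm. Allowing 10% loss, 27 / (1 − 0.10) = 30, so 60 is reproduced. The 10% is back-solved, since the article gives no rate. Power is 84.8% with 30 per arm, 80.7% with 27 and 75.8% with 24. About 3 losses per arm are covered, for power only.

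**2. Who enters each test in its standard form.**

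| Analysis | Needs | Seen at T1, lost before T2 |
|---|---|---|
| t-test, ANCOVA or rank test at T1 | T0, T1 | kept |
| t-test, ANCOVA or rank test at T2 | T0, T2 | dropped |
| Paired test T0-T2 | T0, T2 | dropped |
| Repeated-measures ANOVA on three visits, listwise | T0, T1, T2 | dropped, T1 value included |
| Likelihood-based mixed model | any post-baseline visit | kept |

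**3. Size of the T2 bias.** None of these inputs is in the article; all are assumptions:
- loss after T1 of 10, 20 or 30%, in one arm only
- log-odds of loss rising by 1.5 for each SD of poorer T1 change
- correlation of 0.6 between T1 and T2 change

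If loss depends only on the T1 change, the mean T2 change of those who stay is shifted by

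T2 bias = correlation × (shift in mean T1 change among those who stay).

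Simulation with 400,000 participants per scenario gives shifts in mean T1 change among stayers of 0.118, 0.229 and 0.328 SD:
- 10% loss: 0.6 × 0.118 = 0.07 SD
- 20% loss: 0.6 × 0.229 = 0.14 SD
- 30% loss: 0.6 × 0.328 = 0.20 SD

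The T2 biases simulated directly were 0.072, 0.140 and 0.197 SD, in agreement. Relative to the design effect, 0.07 / 0.784 = 9%, 0.14 / 0.784 = 18% and 0.20 / 0.784 = 26%.

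**4. Range.**
- Halving the log-odds to 0.75 gives T1 shifts of 0.071, 0.138 and 0.203 SD by numerical integration. Multiplied by 0.6, the T2 biases are 0.04, 0.08 and 0.12 SD.
- If both arms lose participants by the same mechanism, at 20% and 10%, the biases largely offset: 0.14 − 0.07 = 0.07 SD. At equal rates they cancel.
- If loss is unrelated to response, there is no bias.

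**5. What the mixed model recovers.** In the same simulation, using the observed T1 value left T2 biases of 0.000, 0.004 and 0.000 SD. This follows from the assumption that loss depends only on the observed T1 value. It would not hold for loss that depends on values never seen.

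**The case against.** The strongest objection is that section 2.8 leaves the method open rather than choosing a wrong one. A repeated-measures analysis may already mean a mixed model on all available visits, and a journal article may leave the analysis set and the handling of missing data to a fuller document that is not shown. This stands in part. The absence of those items is not the point here. The point is that the article does name tests for the between-arm and within-arm comparisons, that these tests drop anyone without the visit, and that its only missing-value rule is attached to another aim.

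A reader might infer more than the text supports:

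- *That efficacy is restricted to participants with complete visits.* The article nowhere says so. Repeated-measures ANOVA is fixed only for the neurophysiological and biochemical data at T0 and T1, and so says nothing about MoCA or FCSRT.
- *That the T1 result is also biased.* Under the assumptions above, the T1 mean would be inflated by 0.12, 0.23 or 0.33 SD (at 20% loss, 0.23 / 0.784 = 29% of the design effect) only if a listwise three-visit ANOVA discarded T1 values for want of T2. That analysis is named for no clinical outcome. The t-test or ANCOVA at T1, which is named, has no bias from later loss.
- *That those who stop the home programme are lost to the analysis.* Section 2.1 has all participants assessed at T0, T1 and T2, with no condition on sessions done. The programme ends at T1, so the loss modelled here is a missed follow-up visit.

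It is also fair to say that no rate, mechanism or imbalance of loss is documented, and that at the roughly 10% implied by the sample size the bias is modest.

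**Conclusion.** The concern holds for T2. Of the methods the article names for MoCA and FCSRT, the between-arm tests at T2 and the paired T0-T2 tests leave out participants without that visit, while the sample size expects some to be lost. If loss depends on T1 response and differs by arm, the T2 contrast is biased towards the arm that loses its poor responders. The size is about 0.07 SD at 10% loss in one arm and 0.14 to 0.20 SD at 20 to 30%, under a fairly strong assumed mechanism; about 60% of that with half the log-odds; and close to nothing with balanced or unrelated loss.

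The claim does not extend to a T1 test that keeps everyone seen at T1, and it does not say that the plan prescribes a completers-only analysis. The case for change is that a better method is available at almost no cost and uses data the trial already collects.

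**What to change.** In section 2.8, name the primary between-arm comparison of MoCA and FCSRT as a likelihood-based mixed model with visit, arm by visit and the baseline value. Include all randomised participants who have any post-baseline value, in their assigned arm, and report the arm difference at T1 and at T2 from that model. This replaces the choice among t-test, ANCOVA and non-parametric test, and any listwise repeated-measures ANOVA, for these outcomes.

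Add a sensitivity analysis that shifts the values assumed for drop-outs over a stated range. The mixed model cannot use anyone seen at neither T1 nor T2, and it does not correct for loss that depends on unseen values; this analysis covers both.

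No new participants, visits or measurements are needed, and section 2.1 already provides for assessing everyone at all three visits. The cost is slightly more analysis work and possibly a smaller estimated effect once partly followed participants contribute.
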